### Outcome measures

Assessment methods (see Table 3) will include standardized self-report questionnaires, task performance measures, and qualitative measures that will be collected at three timepoints (Months 0, 2, and 5). Additionally, at baseline, demographics will be collected for evaluation as potential confounds.

**Table 3 tab3:** Measurement description by domain.

	Type	Content	Category	Cronbach’s alpha	Items
EACQ	Explicit	Caregivers’ experiential avoidance	Relational well-being	0.60–0.71	15 items, 5-point Likert scale
ZBI-12	Explicit	Caregiver burden	Relational well-being	0.69–0.89	12 items, 5-point Likert scale
PAC	Explicit	Positive feelings from care provision	Relational well-being	0.80–0.86	9 items, 5-point Likert scale
IRI	Explicit	Empathic tendencies and feelings	Relational well-being	0.70–0.78	28 items, 5-point Likert scale
FCS	Explicit	Caregivers’ worry about compassion	Relational well-being	0.84–0.92	38 items, 5-point Likert scale
FCI-MS	Explicit	Perceived relationship quality	Relational well-being	>0.90	15 items, 5-point Likert scale
TASIT-SIE	Implicit	Assessing ability to detect sarcastic remarks and lies	Relational well-being	–	17 items, yes/no
HUMOR	Implicit	Assessing humor comprehension	Relational well-being	–	–
SDR	Implicit	Knowledge of social norms around emotional displays	Relational well-being	–	–
DASS-21	Explicit	Depression, anxiety, stress	Psychological well-being	0.86–0.90	21 items, 4-point Likert scale
DERS	Explicit	Trait-level emotion regulation ability	Psychological well-being	0.80–0.89	36 items, 5-point Likert scale
SPANE	Explicit	Positive & negative feelings associated to an experience	Psychological well-being	0.81–0.89	12 items, 5-point Likert scale
SES	Explicit	Perceived self-efficacy	Psychological well-being	–	4 items, 5-point Likert scale
FFMQ-SF	Explicit	Perceived levels of trait mindfulness	Psychological well-being	0.75–0.93	15 items, 5-point Likert scale
SCS-SF	Explicit	Caregivers’ self-compassion	Psychological well-being	>0.86	12 items, 5-point Likert scale
HEMA-R	Explicit	Psychological wellbeing	Psychological well-being	>0.80	10 items, 7-point Likert scale
WHOQOL-BREF	Explicit	Quality of life improvements	Psychological well-being	0.83	Domains, 5-point Likert scale
PES-AD	Explicit	Frequency of events & pleasantness of events	Dementia Patient Lifestyle	0.86–0.95	40 items, 3-point Likert scale

#### Primary outcome: Relational well-being

We hypothesize that participants in the MBSR intervention will experience positive changes in their interpersonal relationships and their ability to perceive and correctly interpret social signals from pre- to post-intervention, and that these changes will be more pronounced than those seen in the active control group. We included a number of measures of caregivers’ relational well-being.

To measure caregivers’ experiential avoidance, the Experiential Avoidance Caregiver Questionnaire (EACQ) will be used (Losada et al., 2014). Participants will rate their tendency to avoid unwanted caregiving experiences on a 5-point Likert scale from 1 (not at all) to 5 (a lot). The EACQ has been shown to have good internal consistency (Cronbach’s alpha; 0.60–0.71). The validity indexes suggest that EACQ is associated with other scales or constructs (e.g., anxiety, depression or alexithymia) in the expected directions. The EACQ may prove to be a useful tool for the identification of avoidance which can be frequently observed in distressed dementia caregivers, and which may explain the maintenance or exacerbation of their high levels of anxiety or stress.

To examine subjective sense of caregiver burden, the Zarit Burden Interview short form (ZBI-12), will be used (Higginson et al., 2010). Participants will rate their perceived burden on a 5-point Likert scale from 0 (*never*) to 4 (*nearly always*). The ZBI-12 has been shown to have good internal consistency (Cronbach’s alpha; 0.69–0.89). No loss of reliability or validity appear to result from reduction of items from the original scale. Consistent with the findings previously reported this measure appears to be an effective measure of caregiver burden (Bédard et al., 2001).

The Positive Aspect of Caregiving (PAC) scale will be used to assess positive feelings resulting from care provision among family caregivers of older adults with functional limitations (Siow et al., 2017). The 9-item PAC scale is a 5-point Likert scale, where participants will rate their positive aspects of caregiving from 1 (disagree a lot) to 5 (agree a lot). Three resulting scores can be derived and used independently in analyses: overall PAC score, SA subscale score (Self-Affirmation), and OL (Outlook-on-Life) subscale. The PAC has been shown to have good internal consistency (Cronbach’s alpha; 0.80–0.86) and is considered a reliable and valid measure for assessing the positive benefits gained by the family caregivers when providing care.

The Interpersonal Reactivity Index (IRI) will be used for assessing caregivers’ empathic functioning (Davis et al., 1980). The IRI yields four subscales of empathy (PT; Perspective Taking-cognitive, FS; Fantasy-cognitive, PD; Personal Distress, EC; Empathic Concern). Participants will rate their empathic tendencies and feelings on a 5-point Likert scale from “*Does not describe me well*” to “*Describes me very well*.” The IRI has been shown to have good internal consistency (Cronbach’s alpha; 0.70–0.78). The IRI subscales will measure caregiver’s empathy as various types of both cognitive processes (perspective taking and fantasy subscales) and affective processes (empathic concern and personal distress subscales).

We will use the Fears of Compassion Scale (FCS), to evaluate caregivers’ worry about compassion to others and themselves (Gilbert, 2014). The FCS yields three subscales (expressing compassion for others, responding to compassion from others, expressing kindness and compassion toward yourself). Participants will rate their worry on a 5-point Likert scale from 0 (*do not agree at all*) to 4 (*completely agree*). FCS has been shown to have good internal consistency (Cronbach’s alpha; 0.84–0.92) and encompasses important implications for therapeutic interventions because affiliative emotions are major regulators of worry-based emotions.

We will use the Mutuality Scale of the Family Care Inventory (FCI-MS), to assess mutuality in relationship between the caregiver and person with dementia, from the caregiver’s perspective (Pucciarelli et al., 2016). Caregivers will rate their perceived relationship quality with their care-recipient on a 5-point Likert scale from 0 (*not at all*) to 4 (*a great deal*). The FCI-MS has been shown to have good internal consistency (Cronbach’s alpha; above 0.90) and is considered a valid and reliable instrument to measure mutuality between patients and caregivers. We will also include direct tests of caregivers’ socioemotional sensitivity and interpersonal cue processing. The capacity to read and correctly interpret contextualized social signals will be assessed *via* The Awareness of Social Inference Test-Social Inference Enriched (TASIT-SIE). TASIT-SIE comprises of conversational exchanges with vignettes containing insincere communication (Honan et al., 2016) and yields multiple scoring subscales on exchanges that involve lying and sarcasm (i.e., doing, saying, thinking, feeling).

The Humor test, developed and validated at UCSF with neurologically healthy older adults, will be used to evaluate humor comprehension. Participants will read predominantly non-verbal cartoon strips missing the last frame, and then select one of four optional endings depicting correct funny (*CF*), straightforward (SF), humorous nonsequitur (HNS), and unrelated nonsequitur (UNS) conclusions. Final scores describe whether participants are sensitive to the “logic” and “surprise” elements of humor.

The Social Display Rules task (SDR), also developed and used at UCSF, will be used to assess caregivers’ knowledge of social norms around emotional displays. Participants will receive descriptions of various social scenarios, and then be asked to imagine the socially appropriate emotional response to them. In each scenario, the socially appropriate response involves altering the immediate emotional reaction. Participants will be asked to select the picture of an emotional face reflecting how they “should” look during the scenario. Subscale scores will be obtained for minimization, intensification, and substitution of an emotion, and a control subscale score will be obtained for selecting the correct emotion when no alteration is socially required.

As part of relational wellbeing, *emotion*, *connectedness*, and *rigidity* statements between caregivers and their care-recipients will be assessed *via* an audio-recorded 10-min semi-structured interview. Verbatim transcripts will be prepared and analyzed using a text analysis software Oedipus Text (Ascher et al., 2010; Connelly et al., 2020). We will assess socioemotional language usage in caregivers across three domains (see Supplementary material):

*Emotion*: Consistent with other studies of emotional language usage (positive and negative), a composite list consisting of words from the emotional lexicon state will be used.*Connectedness:* We will identify the number of pronouns in each of the following three lexical categories, as defined by the pronoun lexicon: we-words (pronouns referring to the couple), me-words (pronouns referring to the speaker) and you-words (pronouns referring to the other spouse).*Rigidity*: We will identify the number of rigid statements (e.g., never) regarding the care recipient’s behavior or characteristics, as defined by the rigidity lexicon.

After initial independent scoring, a consensus review will be performed to confirm reliability and validity of scoring for all analyses. For each domain, mean composites will be generated. In addition, exploratory qualitative analysis will be performed to examine themes in all three domains.

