#### Tertiary outcome: Dementia patient lifestyle/activities

While we predict that direct effects on the caregiver will be the most likely primary and secondary outcomes, we also wish to evaluate the degree to which any changes impact the lives of dementia patients themselves. Because we are not directly enrolling or evaluating patients in the study and will not compromise their confidentiality by identifying them in any way, we will gather indirect evidence of activity changes through caregivers’ subjective reports.

Lifestyle changes in the person with dementia will be measured by asking caregivers to complete the Pleasant Event Schedule-AD (PES-AD). The PES-AD yields two subscales (Frequency of events, Pleasantness of events), and assess the frequency and pleasure the person with dementia receives from daily activities (Logsdon and Teri, 1997). The PES-AD has been shown to have good internal consistency (Cronbach’s alpha; 0.86–0.95).

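### The connectedness pronouns are defined for a conversation between spouses, which does not fit this trial's caregivers or interview; as written, the counts also have no denominator and the composite has no stated direction

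*Protocol article*

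**What the plan says.** All quotes are from the Protocol article. Under Primary outcome: Relational well-being, transcripts of a 10-minute semi-structured interview are scored by text-analysis software in three domains, with further detail referred to Supplementary material that is not shown.

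- **Connectedness:** "We will identify the number of pronouns in each of the following three lexical categories, as defined by the pronoun lexicon". The categories include "we-words (pronouns referring to the couple") and "you-words (pronouns referring to the other spouse"). The third is words for the speaker.
- **Rigidity:** "We will identify the number of rigid statements (e.g., never) regarding the care recipient’s behavior or characteristics".
- **Emotion:** positive and negative usage are named together, and "a composite list consisting of words from the emotional lexicon state will be used".
- **Aggregation:** after independent scoring and a consensus review, "For each domain, mean composites will be generated".

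Other sections describe who is interviewed. Participants admits anyone caring for a person with dementia in their personal life with at least weekly contact. Recruitment, consent, and allocation to interventions has the enrolled caregiver interviewed over Zoom. Tertiary outcome: Dementia patient lifestyle/activities says "we are not directly enrolling or evaluating patients in the study". Data analysis plan lists relationship to the care recipient as a possible confounder and tests each hypothesis at a nominal 0.05.

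**The concern.** The pronoun scheme suits two spouses talking to each other, where *we* is the couple and *you* is the partner. Here a caregiver, who may be a child, sibling or friend, talks about the care recipient to someone else. A scheme that looks for a spouse addressed as *you*, and lists no third-person category, would miss most references to the person the score is meant to concern.

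Two further points arise from the text as written. A number of occurrences grows with how much the caregiver says, and a nominal 10 minutes limits that amount without fixing it. A mean over categories with no stated sign also hides movement between them. At stake is whether one component of the primary domain can be read as connectedness rather than as volume of speech.

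**Working it through.** **1. Definition against design.** No arithmetic is needed here.

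| Scheme assumes | Trial has | Consequence |
|---|---|---|
| A couple (*we*) | Any personal-life caregiver; relationship varies (Participants; Data analysis plan) | No literal referent for non-spouse caregivers |
| The other spouse addressed as *you* | Caregiver interviewed over Zoom; patient not enrolled or evaluated (Recruitment section; Tertiary outcome) | *You* will usually be the interviewer or people in general |
| Three categories: *we*, *me*, *you* | Care recipient spoken about, not to | *He*, *she* and *they* fall in none of the listed categories |

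The middle row's consequence and the spoken-about entry are inferences from the setting. The other entries are stated in the article.

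**2. Counts and the amount of speech.** The article gives no figure to reproduce, so every input below is assumed. Take rates of *we* 1%, *me* 6% and *you* 2% of words, identical for all speakers. The mean count is (0.01 + 0.06 + 0.02) × W / 3 = 0.03 × W.

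| Total words W | Mean count | Mean rate per 100 words |
|---|---|---|
| 800 | 24 | 3.0 |
| 1000 | 30 | 3.0 |
| 1200 | 36 | 3.0 |
| 1500 | 45 | 3.0 |

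From 1200 to 1500 words (+25%) the score rises from 36 to 45 (+25%) with no change in usage.

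How far this matters between people depends on how much word totals vary. A simulation assumed Poisson counts, a mean of 1200 words, a 9% pronoun rate and a between-person CV of the rate of 20%. The correlation of the mean count with total words was 0.41, 0.66, 0.79 and 0.86 for word-total CVs of 10%, 20%, 30% and 40%. For a per-word rate it was about 0.

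For a difference between arms, suppose one arm speaks 15% more at unchanged rates, with CV of the rate c_r = 0.30 and CV of words c_w = 0.20 or 0.30 (all assumed). The CV of the count is √(c_r² + c_w² + c_r²c_w²):

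- c_w = 0.20: √(0.09 + 0.04 + 0.0036) = 0.366, and 0.15 / 0.366 = 0.41 SD
- c_w = 0.30: √(0.09 + 0.09 + 0.0081) = 0.434, and 0.15 / 0.434 = 0.35 SD

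This is a comparison at a single visit, not the planned treatment-by-time test.

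**3. Averaging across categories.** If *we*, *me* and *you* are averaged:

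- before: (10 + 60 + 20) / 3 = 30.0, with a *we* share of 10/90 = 11%
- after: (30 + 40 + 20) / 3 = 30.0, with a *we* share of 30/90 = 33%

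The composite does not move, while separate scores would show the change. Counts cannot be negative, so categories offset within the mean rather than cancel by sign. Rigidity is a single category, so nothing offsets there.

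**The case against.** The strongest reply is that much of this depends on how the text is read.

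- **Raw counts.** The article says number, but does not exclude scaling by words. Supplementary material or the software may supply a denominator, and the planned generalized linear mixed model could carry an offset. Emotion is not described as a count at all. This stands, so the denominator point holds only for the text as written.
- **One composite per domain.** A reader might infer that all categories, and positive with negative words, are averaged into a single score. The plural *composites*, directly after independent scoring, could equally mean one per category or a mean over raters. This stands, so the averaging point is conditional.
- **Definition by referent.** The categories are defined by whom the pronoun refers to, so a *you* addressed to the interviewer would not count. This stands, but the category is then nearly empty, and third-person references still go uncounted in the categories listed.
- **Size.** The speech difference and the CVs are assumed. Caregiver random effects would largely absorb stable differences in talkativeness. That the mindfulness arm would talk more after weekly live sessions is conjecture, since controls also have two group discussions. This stands, although a change in speech that differs by arm would remain in the treatment-by-time term.
- **Weight.** A reader might conclude that the score cannot answer the relational question, or that it hides a predicted shift from *me* to *we*. The article states no such hypothesis. The interview sits beside nine relational instruments in Table 3, in a study described as an exploratory pilot.

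None of these replies removes the conflict between spouse-based definitions and a sample not limited to spouses.

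**Conclusion.** The definitional point holds on the article's own text: the *couple* and *other spouse* categories conflict with who is eligible and who is interviewed. That the care recipient will mostly be named in the third person is a strong inference from the setting, not a stated fact.

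The scoring points hold as written and conditionally. Connectedness and rigidity are numbers with no stated denominator, and the composite has no stated direction. If the three pronoun counts are averaged, the score scales in proportion to words spoken and can hide offsetting shifts completely. No numerical effect on the trial result can be claimed: the figures of 0.41 to 0.86 (correlation) and 0.35 to 0.41 SD only illustrate assumed inputs. This is a worthwhile correction to one component of the primary domain. It does not invalidate that domain.

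**What to change.** Before transcripts are scored:

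1. Redefine the pronoun categories around the caregiver and care recipient, whatever their relationship. *We* means those two people. Third-person references to the care recipient replace *you*-words or are added to them.
2. Score each category as a rate per caregiver word, or use a count model with log total caregiver words as offset.
3. Analyse *we*-, *me*- and care-recipient words separately, and positive and negative emotion words separately. Limit mean composites to averaging within a category or over raters, and say which.

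If Supplementary material already does any of this, a sentence in the article is enough.

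The cost is a change to the lexicon and scoring script. Verbatim transcripts and a consensus review are already planned, and no new data are needed. Deciding whether a *he* or *she* is the care recipient takes some extra coding. Comparability with earlier couple-conversation studies falls slightly. Separate scores also mean more tests at a nominal 0.05: six (three pronoun, two emotion, one rigidity) against three if each domain had one composite. The plan should therefore say which of them is the main connectedness score.

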#### Secondary outcome: Psychological well-being

We hypothesize that the mindfulness-based intervention will have positive effects on participants’ psychological functioning, including their mental health, emotion regulation, and quality of life.

To examine this domain, we will measure overall mental health using the Depression, Anxiety and Stress Scale-21 (DASS-21; Gloster et al., 2008). Participants will rate statements and their application to their own experience during their past week, generating three subscales (depression, anxiety and stress respectively). The DASS-21 has been shown to have good internal consistency (Cronbach’s alpha; 0.86–0.90) and its depression and anxiety subscales show good correlations with self-rating depression scale and state trait anxiety inventory.

The Difficulties in Emotion Regulation (DERS) scale will be used to assess each participant’s trait-level emotion regulation ability (Gratz and Roemer, 2004). The DERS yields six subscales: (a) lack of emotional awareness (*Awareness*; “I am attentive to my feelings,” reverse-scored); (b) lack of emotional clarity (*Clarity*; “I have difficulty making sense out of my feelings”); (c) difficulty regulating behavior when distressed (*Impulse*; “When I’m upset, I become out of control”); (d) difficulty engaging in goal-directed cognition and behavior when distressed (*Goals*; “When I’m upset, I have difficulty getting work done”); (e) unwillingness to accept certain emotional responses (*Non-acceptance*; “When I’m upset, I become angry at myself for feeling that way); and (f) lack of access to strategies for feeling better when distressed (*Strategies*; “When I’m upset, I believe there is nothing I can do to feel better”). Overall, the DERS has high internal consistency (Cronbach’s alpha; 0.80–0.89), good test–retest reliability, and predictive validity. However, a wide array of follow up studies (Hallion et al., 2018) highlight that the Awareness subscale seem to show relatively poor psychometric properties, concluding that the DERS is psychometrically stronger when the *Awareness* subscale is excluded.

We will use the Scale of Positive and Negative Experiences (SPANE), to assess participants feelings’ valence (positive or negative) toward experience (Diener et al., 2009). The SPANE gives three scores: (a) summed positive (SPANE-P), (b) negative scale (SPANE-N) score, and (c) the two scores combined by subtracting the negative from the positive score, and the resulting SPANE-B scores. SPANE-B shows balance between positive and negative scores. The SPANE has good reliability and convergent validity with other measures of emotion, well-being, happiness, and life satisfaction. The three subscales have high internal consistency (Cronbach’s alpha; 0.81–0.89).

To measure caregivers’ self-efficacy (Merrilees et al., 2020), we will use the Care Ecosystem Self Efficacy Scale (SES).

Characteristics of mindfulness will be assessed *via* the Five Facet Mindfulness Questionnaire-Short Form (FFMQ-SF), yielding five subscales (Observing, Describing, Acting with awareness, Nonjudging, Reactivity). Participants will rate phrases according to their perceived mindfulness (Bohlmeijer et al., 2011). The FFMQ-SF accurately identifies varying levels of trait mindfulness and has been shown to have good internal consistency (Cronbach’s alpha; 0.75–0.93). Importantly, studies utilizing this instrument report increases in individual’s FFMQ scores with participation in MBSR programs (Baer et al., 2012).

The Self-Compassion Scale-Short Form (SCS-SF) will be used to assess caregivers’ self-compassion (Neff, 2003). The SCS-SF yields six subscales (Self-Kindness, Self-Judgment, Common Humanity Items, Isolation, Mindfulness, Over-identification). The SCS-SF has been shown to have good internal consistency (Cronbach’s alpha; above 0.86). Research has shown that self-compassion is associated with psychological well-being and is an important protective factor that fosters emotional resilience, with higher levels of self-compassion to be typically related to greater psychological health as demonstrated by less depression and anxiety (Raes, 2011).

Psychological well-being will be measured *via* the Hedonic and Eudaimonic Motives for Activities-Revised (HEMA-R) scale (Huta and Ryan, 2009). The HEMA-R yields two scoring subscales: 1. hedonic; personal importance of pleasure and absence of pain and 2. eudaimonic; personal importance of authenticity, excellence, and growth. Participants will rate to what extent they experience their lives as valuable. The HEMA-R has been shown to cohere as a single distinct factor and has good internal consistency (Cronbach’s alpha; above 0.80). Eudaimonic and hedonic motives exhibit beneficial effects on a wide range of positive outcomes such as emotion regulation, coping strategies and well-being (Ortner et al., 2018).

An additional measure pertaining to psychological well-being will be the WHO-quality of life (WHOQOL-BREF) questionnaire. The WHOQOL-BREF will be used to assess quality of life improvements in domains of physical health, psychological, social relationships, and environment (THE WHOQOL GROUP, 1998). The WHOQOL-BREF has been shown to have good internal consistency (Cronbach’s alpha; 0.83) and can be used to measure caregiver’s subjective experiences of their own physical, mental and social well-being.

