Even with these caveats, however, we believe this study represents an important step in a much-needed line of investigation. Adaptation of existing, effective interventions for use with caregivers is a novel but important healthcare intervention. Evidence suggests that caregivers of persons with dementia are experiencing long-term, intensive stress (Connell et al., 2001; Sörensen and Conwell, 2011; George et al., 2020). Because mindfulness-based interventions are based in the foundational features of nonjudgmental awareness and acceptance of negative emotions and circumstances, they have untapped potential to positively impact the wellbeing of dementia caregivers (Jaffray et al., 2015).

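### HEMA-R is presented as measuring psychological well-being, but the protocol describes it as a scale of motives, so a difference on it is at most indirect support for hypothesis B

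*Protocol article*

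**What the plan says.** In the protocol article, under the secondary outcome, the paragraph on this instrument opens with "Psychological well-being will be measured" and names as the means the "Hedonic and Eudaimonic Motives for Activities-Revised (HEMA-R) scale". Table 3 (Outcome measures) gives psychological wellbeing as its content, places it in the psychological well-being category, and lists it as "10 items, 7-point Likert scale".

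The same paragraph then describes the scale in four further ways:

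- The two subscales are "hedonic; personal importance of pleasure and absence of pain and 2. eudaimonic; personal importance of authenticity, excellence, and growth".
- The response task is "Participants will rate to what extent they experience their lives as valuable".
- On structure, "The HEMA-R has been shown to cohere as a single distinct factor".
- On the link to outcomes, "Eudaimonic and hedonic motives exhibit beneficial effects on a wide range of positive outcomes such as emotion regulation, coping strategies and well-being".

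Hypothesis B, at the end of the Introduction, predicts greater psychological well-being in the mindfulness arm. The Data analysis plan models every outcome measure with treatment, time and their interaction, and judges each hypothesis separately at a nominal 0.05.

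**The concern.** How much a person values pleasure or growth is a different quantity from how well that person is. If HEMA-R scores the former, its label in the text and in Table 3 is wrong. A treatment-by-time effect on it would then be reported as a change in well-being when it shows a change in priorities.

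What is at stake is the reading of one result. The pilot sets out to establish preliminary effect sizes for all its measures (Sample size calculation). A HEMA-R effect size filed under well-being could therefore carry the wrong construct into the planning of a later trial.

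**Working it through.** No arithmetic applies beyond a count, so the check sets the statements side by side.

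1. **Label.** The opening sentence and the Table 3 content entry both say that the scale measures psychological well-being.
2. **Name.** The instrument's title says motives for activities. This disagrees with step 1.
3. **Subscales.** Both are defined by personal importance. A caregiver can attach great importance to pleasure or growth and be doing badly, or little and be doing well. This agrees with step 2 and disagrees with step 1.
4. **Relation to well-being.** The protocol lists well-being among the outcomes on which these motives have an effect ("Eudaimonic and hedonic motives exhibit beneficial effects on a wide range of positive outcomes such as emotion regulation, coping strategies and well-being"). Something that acts on well-being is treated there as distinct from it. This again agrees with step 2.
5. **Response task.** "Participants will rate to what extent they experience their lives as valuable" is a rating of experience. It is the one descriptive sentence that could support step 1, but it fits neither the name nor either subscale definition.
6. **Score.** A single factor is reported next to two scored subscales, so the paragraph does not make clear which score would carry a well-being statement.

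Three statements (steps 2 to 4) describe motives. The label and the response sentence (steps 1 and 5) describe well-being or something near it. They cannot all be right.

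**How far it reaches.** Table 3 puts eight instruments in this category: DASS-21, DERS, SPANE, SES, FFMQ-SF, SCS-SF, HEMA-R and WHOQOL-BREF. HEMA-R is 1 of 8. Several others are also not direct well-being scores, but Table 3 labels them for what they measure: trait mindfulness for FFMQ-SF, self-compassion for SCS-SF, self-efficacy for SES, and emotion regulation for DERS. HEMA-R is the only one whose content entry is well-being itself. DASS-21, SPANE and WHOQOL-BREF cover mental health, feelings and quality of life, so hypothesis B can be addressed without it.

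**The case against.** The best defence is that the domain is deliberately broad. The secondary hypothesis speaks of psychological functioning, and the category takes in mindfulness and self-compassion, the latter justified as protective and as associated with well-being. Including a determinant of well-being is consistent with that design. This stands as a reason to keep HEMA-R in the trial. It does not justify labelling it as well-being, which Table 3 does for no other determinant.

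A second objection is that the documents cannot settle what respondents actually rate, because the instrument is not shown. That stands too. It supports reconciling the sentences and makes the motives reading conditional on the subscale definitions being the correct ones.

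Two stronger readings are tempting, and the documents support neither.

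- **That the direction of benefit is reversed.** A reader might set the importance of absence of pain against the Discussion's account of mindfulness as "nonjudgmental awareness and acceptance of negative emotions and circumstances" and infer that a successful course would lower the hedonic score. Accepting negative emotions does not imply valuing pleasure less. The Introduction names savoring of positive experiences as a mechanism, and Session 3 in Table 2 trains appreciation of pleasant moments. The protocol states no direction for either subscale, but its sentence on the beneficial effects of these motives implies that higher is favourable.
- **That HEMA-R decides hypothesis B.** A reader might infer that a fall would count as worse well-being and so against the hypothesis. The Data analysis plan has no rule by which any single scale decides the hypothesis. HEMA-R is also not the only measure, since WHOQOL-BREF is introduced as a further one in the same domain.

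Finally, the instrument's full name would appear in any report, so a careful reader could see that motives were measured. That limits the harm but does not correct the protocol's wording.

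**Conclusion.** The inconsistency is real and can be shown from the protocol article alone. The label says well-being, while the name, the subscale definitions and the stated relation to outcomes say motives. The response description fits neither the name nor the subscales. A between-arm HEMA-R difference should be read as a change in motives, which is at most indirect support for hypothesis B, and not as a gain or loss in well-being.

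The size is minor. One of eight secondary instruments is affected, in a study described as an exploratory pilot. The primary outcome, sample size and randomisation are untouched. The conclusion assumes that the name and subscale definitions describe the scale correctly. If the response sentence is the accurate one, the definitions need correcting instead, and the paragraph must be reconciled either way.

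**What to change.** - Check the HEMA-R paragraph against the questionnaire in use and reconcile the response description with the subscale definitions. State which scores will be reported, given the single-factor remark.
- Change the Table 3 content entry for HEMA-R to hedonic and eudaimonic motives for activities, and change the opening sentence of the paragraph to match.
- Report the two subscales as exploratory process measures, and do not describe a difference on them as a change in well-being.
- Rest the well-being conclusion on WHOQOL-BREF, SPANE-B and DASS-21, which are already collected.

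The cost is wording and reclassification. The questionnaire is still administered, and no data or participant burden is added. One fewer measure counts directly toward hypothesis B.
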